### 15.5.2 Analysis Variables

Primary Endpoint: DLT

Secondary Endpoint: Adverse drug reactions, RFS, DCR,

### 15.5.3 Statistical Method

For the primary endpoint, the DLT Analysis Set (DAS) included all participants who were in the DLT evaluation period and either completed the DLT assessment or experienced a DLT during the evaluation period. This analysis set will be used for the analysis and summary of DLT events. DLT Rate = ( Number of participants with ≥1 DLT / Total evaluable participants in DAS)×100%. 95% CI will be computed using the Clopper-Pearson method.

For Secondary Endpoints, such as RFS, the median value and 95% CI are estimated and survival curves are obtained using the Kaplan-Meier method. The log-rank test is used to compare the survival between the two groups. DCR with 95% CI are calculated, and comparisons between treatment groups are performed using a Cochran-Mantel-Haenszel (CMH) test or chi-square test. Two independent samples will be compared for the differences between the two groups in QoL scores by the t-test or Wilcoxon rank sum test.

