# 3. Study Endpoints

## 3.1 Primary Endpoints

Incidence and frequency of DLT

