## 4.3 Dose Escalation Principles

(1) Following the "3+3 principle", that is, three subjects were enrolled in each group, and the safety and tolerability of the first cycle were observed after administration. If no DLTS occurred, the trial proceeded to the next dose level according to the established dose-escalation protocol. If one DLT occurred, three more subjects were added at that dose level. When no new DLT occurred, the trial was continued at the next dose level. If ≥ 2 DLTS occurred, the dose level preceding that dose level was defined as MTD.

(2) The subjects with DLT were treated by the investigators according to the clinical diagnosis and treatment standards, and the dose could be delayed for no more than 2 weeks, the original dose could be maintained, or the dose level could be lowered to continue the next cycle. If no DLT occurred in the three patients enrolled in the first dose group during the observation period, the subsequent treatment was escalated to the second dose level.

(3) If more than one patient experienced DLT at the prespecified lowest dose, the lower dose was explored by the investigator.

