# 13. Study Assessments

## 13.1 Efficacy assessment

The primary analysis of this study utilizes tumor assessments conducted per RECIST v1.1 criteria. All study-related decisions during trial execution will be based on local investigators' assessments of imaging results, participants' clinical status and relevant laboratory/ diagnostic findings.

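### The primary DLT rate in Protocol 15.5.3 pools both dose levels and both arms, so the reported estimate and its interval describe neither dose

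*Protocol*

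**What the plan says.** Section 3.1 gives the primary endpoint as "Incidence and frequency of DLT" and names no dose level or arm. Section 15.5.3 turns this into a formula, "Number of participants with ≥1 DLT / Total evaluable participants in DAS", expressed as a percentage, and adds that "95% CI will be computed using the Clopper-Pearson method". The analysis set is just as undivided: "the DLT Analysis Set (DAS) included all participants who were in the DLT evaluation period" and who either completed the assessment or had a DLT. The synopsis and section 15.5.2 add no split.

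The design has more structure than that. Section 4.2 uses two irinotecan liposome levels, 37.6 and 56.5 mg/m². Section 4.1 has two arms: neoadjuvant treatment of tumours that TURBT cannot remove (Arm A), and treatment after TURBT (Arm B). Section 5 plans 6–9 participants per arm, 12–18 in all. Section 4.3 applies a 3+3 scheme at each level: "If ≥ 2 DLTS occurred, the dose level preceding that dose level was defined as MTD".

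Two further wordings bear on the endpoint. Item (1) of section 4.3 counts DLTs, while item (3) counts people: "If more than one patient experienced DLT at the prespecified lowest dose". Section 13.1 says "The primary analysis of this study utilizes tumor assessments conducted per RECIST v1.1 criteria", although DLT is the primary endpoint everywhere else.

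**The concern.** A dose-escalation trial asks how often DLTs occur at each dose. A rate taken over the whole DLT Analysis Set answers another question: how often they occurred across whatever mix of doses and arms was enrolled. That mix is an outcome of the escalation process, because cohorts are expanded or stopped according to the DLTs seen. The pooled figure is therefore an allocation-weighted average and not the risk at either level.

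At stake is the trial's headline result. A reader choosing a dose for a later study would be given a percentage and an exact interval that belong to neither candidate. If DLTs become more frequent with dose, the pooled rate understates the higher level and overstates the lower.

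**Working it through.** **Inputs.** Two dose levels (section 4.2); 2 × 6 = 12 to 2 × 9 = 18 participants, which reproduces the total in section 5; Clopper-Pearson 95% intervals (section 15.5.3). The protocol gives no DLT counts or expected rates, so those below are assumptions chosen for illustration.

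**Interval formula.** For x affected participants out of n, the lower limit is the 2.5% quantile of Beta(x, n − x + 1), or 0 if x = 0. The upper limit is the 97.5% quantile of Beta(x + 1, n − x).

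**Pooled against per-level results**

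| 37.6 mg/m² | 56.5 mg/m² | Pooled, as 15.5.3 is written | Lower level | Higher level |
|---|---|---|---|---|
| 0/6 | 2/6 | 2/12 = 16.7% (2.1–48.4%) | 0% (0–45.9%) | 33.3% (4.3–77.7%) |
| 0/12 | 2/6 | 2/18 = 11.1% (1.4–34.7%) | 0% (0–26.5%) | 33.3% (4.3–77.7%) |
| 0/9 | 2/3 | 2/12 = 16.7% (2.1–48.4%) | 0% (0–33.6%) | 66.7% (9.4–99.2%) |
| 0/6 | 4/6 | 4/12 = 33.3% (9.9–65.1%) | 0% (0–45.9%) | 66.7% (22.3–95.7%) |

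Rows 1 and 2 have identical data at the higher level, yet the pooled rate falls from 16.7% to 11.1% because six more unaffected participants sit at the lower level. Rows 1 and 3 give the same pooled result although the observed rate at the higher level doubles. Row 4 would arise if each arm ran its own 3+3 and saw 0/3 and then 2/3; that is 12 participants, the planned minimum.

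**Expected value.** With true rates p_L and p_H and n_L and n_H participants, the expected pooled rate is (n_L·p_L + n_H·p_H)/(n_L + n_H).

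- p_L = 5%, p_H = 40%: with 6 + 6 participants, (0.3 + 2.4)/12 = 22.5%; with 9 + 3, (0.45 + 1.2)/12 = 13.8%.
- p_L = 10%, p_H = 50%: with 6 + 6, (0.6 + 3.0)/12 = 30%; with 9 + 3, (0.9 + 1.5)/12 = 20%.

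The true risks are fixed within each line; only the allocation changes.

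**No DLTs at all.** Pooling leaves the point estimate at 0%, but the upper limit becomes 26.5% (0/12) where 6 participants at one level support only 45.9% (0/6).

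**Participants who receive both levels.** Section 4.2 starts the first three Arm B participants at 37.6 mg/m² and, if treatment is well tolerated, moves them to 56.5 mg/m² in the second cycle. Section 4.3 observes the first cycle for escalation; section 15.5.3 does not say to which dose a second-cycle DLT belongs. If second-cycle events count, these three enter both denominators and the per-level samples overlap. A bare split by dose would leave this open.

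**The case against.** The strongest reply is that the pooled rate drives no decision. Section 4.3 works level by level, and two affected participants in a cohort of three at 56.5 mg/m² would already place that level above the MTD, whatever 15.5.3 later reports. This stands. A reader might infer that pooling lets a toxic dose go unnoticed during the trial; the protocol does not support that.

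A second reply is that the formula is generic and that by-dose tables are ordinary content for a SAP, which may exist. It stands in part: nothing in 15.5.3 forbids such tables. But the protocol does not leave the estimator open. It states a total denominator and an interval method for the primary endpoint, and additional tables would not change which figure is primary.

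Third, the distortion has no fixed direction. The higher dose looks safer only if the observed rate rises with dose, and the 0/6 against 4/6 example is an extreme one. Both points are fair, which is why milder and no-event cases are shown.

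Two other stronger readings should be resisted. Taken literally, item (1) of section 4.3 would let one participant with two toxicities set the MTD. The 3+3 label and the references to patients elsewhere in 4.3 make shorthand for affected participants the more natural reading, and the protocol gives no basis for estimating how often the difference would matter. Nor does section 13.1 make tumour response the primary endpoint: its sentence sits under an efficacy heading, and sections 3.1, 15.5.2 and 15.5.3 all name DLT.

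**Conclusion.** The point holds as a fault in the reported primary estimate, not in the escalation decisions. As written, section 15.5.3 yields one rate over at most 12–18 participants that mixes two doses and two clinical settings and does not match the per-level logic of section 4.3. In the examples, 33.3% at the higher level is reported as 16.7% or 11.1%, and 66.7% as 33.3% or 16.7%, depending on the allocation. These sizes rest on assumed DLT counts and rates, and the direction rests on toxicity rising with dose. The dependence on allocation needs only that the rates differ between levels.

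The mixed counting units in section 4.3 are a separate inconsistency to reconcile. The primary-analysis wording in section 13.1 is editorial.

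**What to change.** In section 15.5.3, define the primary estimate as the proportion of evaluable participants with at least one DLT, with its Clopper-Pearson 95% interval, at each dose level received during the DLT evaluation period. Show it by arm and with the arms combined within dose. State how a second-cycle DLT after within-participant escalation in Arm B is attributed, in the numerator and in the denominator. Keep any rate pooled over doses as a labelled supplement.

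Separately, ask the sponsor to reconcile section 4.3(1), which counts DLTs, with 4.3(3) and 15.5.3, which count patients or participants; which unit governs escalation is for the sponsor to settle. In section 13.1, refer to the efficacy analysis instead of the primary analysis.

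The cost is wording only, with no change in sample size. The per-level intervals will be wide (0/3 gives 0–70.8%, 0/6 gives 0–45.9%) and should be read as descriptive. That is the precision that this number of participants per dose can give.

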| Endpoints | 1. Primary Endpoints:  Incidence and frequency of Dose-Limiting Toxicity (DLT)  2. Secondary Endpoints:  (1) Adverse drug reactions;  (2) Recurrence-Free Survival (RFS);  (3) Disease Control Rate (DCR);  3. Tumor Response Evaluation (per RECIST 1.1 criteria):   - Complete Response (CR): Disappearance of all target lesions; no new lesions. - Partial Response (PR): ≥30% decrease in the sum of diameters of target lesions. - Stable Disease (SD): Neither sufficient shrinkage to qualify for PR nor sufficient increase to qualify for PD. - Progressive Disease (PD): ≥20% increase in the sum of diameters of target lesions or appearance of new lesions. |
| Study Procedures | 1. Arm A: TURBT unresectable  If the recurrent tumor can't be excised by TURBT, participants will be assigned to this arm. Participants in this arm will complete the neoadjuvant therapy with Irinotecan liposome (intravenous injection, once every two weeks for 1 month, dose increasing regimen: 37.6 mg/m^2^ and 56.5mg/m^2^) and Epirubicin (intravesical instillation, once a week for 1 month, 50 mg), and the therapeutic effect was evaluated by pelvic enhanced MRI and cystoscopy. Judged by two senior urologists, patients with complete response and partial response were treated with TURBT and intravesical therapy. Patients with stable disease or progressive disease received subsequent therapy at the investigator's discretion. Participants will visit the clinic once every 2 weeks for checkups and tests.  2. Arm B: TURBT resectable  If the recurrent tumor can be excised by TURBT, participants will be assigned to this arm (Arm B). Participants in this arm will complete TURBT with immediate intravesical instillation of Epirubicin (50 mg) within 24 hours after surgery. During the induction phase (the first 1 month after surgery), participants will receive the combined therapy with irinotecan liposome (intravenous injection, once every two weeks for 1 month, dose increasing regimen: 37.6 mg/m^2^ and 56.5mg/m^2^) and Epirubicin (intravesical instillation, once a week for 1 month, 50 mg). In the next 6 months, participants will continue the intravesical instillation treatment with Epirubicin (once a month, 50 mg). Participants will visit the clinic once every 2 weeks for checkups and tests in the first month, and once every 3 months after the first month. |

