## 3.2 Secondary Endpoints

(1) Adverse drug reactions: Any noxious, unintended response to the investigational drug(s) (Irinotecan liposome + Epirubicin) at any dose, causally related to treatment (per WHO-UMC causality assessment criteria).

(2) Recurrence-Free Survival (RFS): Time from treatment initiation to histologically confirmed tumor recurrence, radiologic progression or death from any cause.

(3) Disease Control Rate (DCR): Proportion of patients achieving complete response (CR), partial response (PR) and stable disease (SD).

Note: Tumor Response Evaluation (per RECIST 1.1 criteria):

- CR: Disappearance of all target lesions; no new lesions.
- PR: ≥30% decrease in the sum of diameters of target lesions.
- SD: Neither sufficient shrinkage to qualify for PR nor sufficient increase to qualify for progressive disease (PD).
- PD: ≥20% increase in the sum of diameters of target lesions or appearance of new lesions.

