## 4.1 Overall design

Enrolled patients with anthracycline-resistant recurrent NMIBC will first undergo enhanced pelvic-abdominal MRI and cystoscopy to collect imaging and pathological data. Two senior urologists will determine whether the tumor is resectable via TURBT. If unresectable (Arm A), patients will receive neoadjuvant irinotecan liposome combined with Epirubicin per the dose-escalation protocol. Post-treatment efficacy will be assessed by contrast-enhanced pelvic-abdominal MRI. For patients with CR and PR, TURBT with intravesical therapy was performed following confirmation by two independent senior urologists. For patients with SD or PD, subsequent therapies were determined by the investigator’s discretion. If resectable (Arm B), TURBT will be performed followed by immediate intravesical Epirubicin (50 mg) instillation within 24 hours postoperatively. During the induction phase (weeks 1-4 post-TURBT), the treatment with irinotecan liposome combined with Epirubicin will be completed according to the dose - escalation regimen. During the maintenance phase (months 1-6 post-TURBT), intravesical maintenance instillation of Epirubicin will be conducted once a month for a total of 6 cycles. The safety and adverse reactions will be followed up from the induction phase, and the tumor recurrence will be assessed by pelvic and abdominal enhanced MRI and cystoscopy after combination treatment.

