## 15.5 Statistical Analysis

### 15.5.1 Analysis datasets

(1) Full Analysis Set (FAS):

The Full Analysis Set (FAS) consists of all study participants who signed the ICF, were enrolled in the study, and received at least one dose of the investigational drug. The FAS serves as the primary analysis set for efficacy endpoints in this study. For cases where the full treatment course was not observed, the last observation carried forward (LOCF) method will be applied to impute missing data for the final analysis.

(2) Per-protocol set (PPS):

PPS will be defined as all subjects who met the trial protocol, did not take prohibited drugs, with favorable compliance, and completed CRF. No imputation of missing data. Efficacy analysis was conducted based on PPS populations.

(3) Safety analysis set (SS):

The SS population will serve as the population for the safety analysis. All randomized subjects have received at least one dose of the research drug and have a post-administration safety record.

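### The planned between-group tests on RFS and DCR compare arms formed by resectability that receive the same study combination, so they cannot show an effect of the study treatment

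*Protocol*

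**What the plan says.** Section 4 calls the study single-arm, and no section describes a randomisation procedure. Allocation follows a clinical judgement (section 4.1): "Two senior urologists will determine whether the tumor is resectable via TURBT". The synopsis says of Arm A: "If the recurrent tumor can't be excised by TURBT, participants will be assigned to this arm". For the other arm, section 4.1 says: "If resectable (Arm B), TURBT will be performed followed by immediate intravesical Epirubicin (50 mg) instillation within 24 hours postoperatively". Both arms then receive irinotecan liposome with intravesical epirubicin (sections 4.1 and 4.2).

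Section 3.2 defines RFS as "Time from treatment initiation to histologically confirmed tumor recurrence, radiologic progression or death from any cause". It defines DCR as the proportion with CR, PR or SD under RECIST 1.1, where for example "CR: Disappearance of all target lesions; no new lesions". Neither endpoint is limited to one arm.

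Section 15.5.3 plans for RFS: "The log-rank test is used to compare the survival between the two groups". For DCR it says "comparisons between treatment groups are performed using a Cochran-Mantel-Haenszel (CMH) test or chi-square test". It also plans a two-group t-test or Wilcoxon test on QoL scores. The synopsis repeats all three. Section 15.5.1 describes the safety set thus: "All randomized subjects have received at least one dose of the research drug". Section 5 plans 6-9 participants per arm, 12-18 in total.

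**The concern.** A p-value from a comparison labelled as between treatment groups will be read as evidence about treatment. Here the grouping variable is itself a likely prognostic factor, and it also decides when surgery happens. No group goes without the study combination. A difference in RFS or DCR could therefore arise with no differential drug effect at all, and a null result would say nothing about the drugs either.

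The two endpoints also do not carry the same meaning in both arms, so the comparison would be of unlike quantities even if the arms were prognostically alike. Efficacy is part of the first study objective, and RFS and DCR are the only efficacy endpoints listed, so how they are reported matters.

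**Working it through.** **1. What differs between the arms** (synopsis; sections 4.1, 4.2 and 4.4)

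| | Arm A | Arm B |
|---|---|---|
| Entry to arm | judged unresectable | judged resectable |
| Study combination | yes | yes |
| TURBT | after the combination, in CR/PR only | before the combination |
| Other epirubicin | intravesical therapy with TURBT after CR/PR (agent not named) | one instillation within 24 hours of TURBT, then six monthly instillations |
| Assessment after the combination | response | recurrence |

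The study combination is the element the arms share. Everything else in the table differs, so the contrast cannot isolate it.

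**2. Do the endpoints transfer?**

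- DCR: CR, PR and PD are defined through target lesions or new lesions. In Arm B the tumour has been resected before the combination starts, so there is no shrinkage for the drugs to produce. Section 4.1 itself assesses Arm B for recurrence.
- RFS: in Arm A the tumour is in place at time zero. A participant with stable residual tumour has no event, although never tumour-free. Because radiologic progression and death count as events, the quantity can be calculated, but it is a progression-type time. In Arm B the clock starts at or after tumour removal.

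**3. Size of the DCR table**

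The plan's own figure reproduces: 2 × 6 = 12 and 2 × 9 = 18. It is a sum only; no alpha, power or effect size is given.

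With n per arm, each expected count is half of its column total. The two column totals (controlled, not controlled) add to 2n, so the smaller is at most n and its two expected counts are at most n/2. That is 3.0 for n = 6 and 4.5 for n = 9.

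Assumed table: Arm A 3/6 controlled, Arm B 6/6; column totals 9 and 3.

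- Uncorrected chi-square: 12 × (3×0 − 3×6)² / (6×6×9×3) = 3888/972 = 4.00, p = 0.046.
- One-stratum CMH: (3 − 4.5)² / [6×6×9×3 / (12² × 11)] = 2.25/0.6136 = 3.67, p = 0.056.
- Yates-corrected chi-square: 12 × (18 − 6)² / 972 = 1.78, p = 0.18.
- Fisher, two-sided: 2 × C(6,3) × C(6,6) / C(12,9) = 40/220 = 0.18.

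The same data fall on either side of 0.05 depending on a choice that section 15.5.3 leaves open.

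**4. How often would the tests reject with no drug difference?**

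Assumptions: two-sided alpha 0.05; arms differing only through surgery or prognosis. The chi-square is uncorrected and exactly enumerated. The log-rank is simulated with 4,000 runs, exponential times and no censoring.

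| Assumed difference | 6 per arm | 9 per arm |
|---|---|---|
| DCR 70% v 100%, chi-square | 26% | 27% |
| DCR 50% v 90%, chi-square | 39% | 50% |
| DCR 50% v 100%, chi-square | 66% | 75% |
| Prognostic HR 2, log-rank | 21% | 30% |
| Prognostic HR 3, log-rank | 41% | 58% |

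For 80% power the log-rank test would need 4(1.96 + 0.84)²/(ln HR)² events: 66 at HR 2 and 27 at HR 3, against 12-18 participants.

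**5. Related wording**

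- Safety set: section 15.5.1 refers to randomised subjects, and section 12.1 ends screening at randomisation. Nobody is randomised.
- QoL: it is not an endpoint in sections 3.1, 3.2 or 15.5.2, and no QoL item appears in the visit lists of sections 12.1 to 12.6.

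**The case against.** Several stronger readings are tempting, and the protocol does not support them.

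- *Each endpoint is meaningful in one arm only.* For DCR as a measure of drug response this is close to right. For RFS it goes too far: progression and death are events, so Arm A yields a usable progression-type time. It is misnamed and not comparable with Arm B, but it is not meaningless.
- *Arm B will score 100% on DCR because of surgery.* No section says Arm B participants are scored as CR, and a new lesion after induction could count as PD. DCR there is ill-defined, not fixed at 100%; the 6/6 and 100% figures above are assumptions.
- *A pooled DCR will credit the drugs with surgical results.* The protocol does not clearly plan a pooled DCR.
- *The planned test gives p = 0.046.* Only the uncorrected chi-square does; CMH is named first and no correction is specified. The approximation is doubtful rather than shown to be invalid.
- *The safety set is empty.* Literally yes, but the FAS in the same section is defined by enrolment and dosing, so this reads as wording to correct.

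It can also be said that section 15.5.3 does not define its two groups, and section 4.3 uses the word group for dose level. Arms A and B remain the natural reading, since the sample size is set per arm. Dose groups would not be clean either, because the first three Arm B participants may move to the higher dose in the second cycle (section 4.2).

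Two limits stand. The study flowchart mentioned in section 12 is not shown, so the QoL remark covers only the listed visits. And these are secondary endpoints in a small exploratory study, with no hypothesis or dose decision attached to the tests. Deferral to an SAP is no answer, because the protocol itself fixes the tests.

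**Conclusion.** The point holds as stated in the heading. The between-group tests on RFS and DCR cannot be read as tests of the study treatment, whatever their result. This conclusion rests on the allocation rule and the shared combination, not on any assumed rate. It takes the two groups to be Arms A and B.

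The illustrations show the size. Under assumed differences due only to surgery or prognosis, the tests reject in about 21% to 75% of trials. In one assumed table p ranges from 0.046 to 0.18 according to the version of the test. DCR does not measure drug response in Arm B, and Arm A RFS is a progression-type time.

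Severity: should be fixed. The primary DLT analysis, with its Clopper-Pearson interval, is unaffected.

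**What to change.** In section 15.5.3 and the synopsis:

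- Delete the between-group log-rank, CMH/chi-square and QoL tests. Report each arm descriptively.
- Report DCR in Arm A only, with an exact (Clopper-Pearson) confidence interval.
- Report RFS in Arm B. Label the Arm A time-to-event result as progression-free time from treatment start, and say so in section 3.2.

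In section 15.5.1, define the safety set as all participants who received at least one dose, and remove the reference to randomisation there and in section 12.1.

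The cost is wording, through an amendment that section 17 sends to the Ethics Committee. No participants, visits or eligibility changes are needed. The sponsor loses p-values that have no treatment interpretation.

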# 5. Sample Size

Both arms are expected to enroll 6-9 subjects each, with a total planned enrollment of 12-18 subjects.

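### The between-arm DCR comparison is fixed as a CMH or chi-square test at 6-9 patients per arm, where either test can exceed a 5% error rate and the two can disagree on the same data

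*Protocol*

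**What the plan says.** Section 3.2 defines the endpoint as a proportion: "Disease Control Rate (DCR): Proportion of patients achieving complete response (CR), partial response (PR) and stable disease (SD"). Section 5 gives the size: "Both arms are expected to enroll 6-9 subjects each, with a total planned enrollment of 12-18 subjects". Section 4.1 sets how patients reach the arms: "Two senior urologists will determine whether the tumor is resectable via TURBT". For the comparison of the two arms, section 15.5.3 says that "comparisons between treatment groups are performed using a Cochran-Mantel-Haenszel (CMH) test or chi-square test", and the synopsis has the same sentence.

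Neither place names a continuity correction, a rule for small expected counts, an exact alternative, a stratification factor for the CMH test, or a rule for choosing between the two tests. No significance level is stated for any test. The same section uses an exact method for the DLT rate: "95% CI will be computed using the Clopper-Pearson method".

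**The concern.** Both named tests take their p-value from a chi-square distribution that holds only approximately, and least well in small tables. With 6-9 patients per arm, the chance of a significant result when the arms have the same true DCR may differ from the nominal level. A result reported as significant could then come from the approximation alone. Because the plan allows either test without a rule, the choice could also decide on which side of 0.05 the result falls. The choice of test is not left to a later document here: the protocol makes it.

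**Working it through.** **Inputs.** Arm sizes n1 and n2 from 6 to 9 (section 5), which give totals of 2 × 6 = 12 to 2 × 9 = 18, as the protocol states. A binary endpoint (section 3.2). A CMH or chi-square test (section 15.5.3). The protocol gives no alpha, power or assumed DCR, so there is no planned error rate to reproduce.

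**Assumptions.** Two-sided 5% level; a common true DCR scanned from 0.001 to 0.999; CMH without strata.

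**Step 1: expected counts.** With m responders among N = n1 + n2, the smallest expected count is min(n1, n2) × min(m, N − m) / N. Its largest attainable value is 9 × 9 / 18 = 4.5 at 9 versus 9, 8 × 8 / 16 = 4.0 at 8 versus 8, 6 × 6 / 12 = 3.0 at 6 versus 6, and 6 × 7 / 15 = 2.8 at 6 versus 9. No pair reaches 5.

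**Step 2: true error rate.** For a 2×2 table with a/n1 and b/n2 responders, let d = |a(n2 − b) − b(n1 − a)|. Then

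- Pearson: X² = N d² / [n1 n2 m (N − m)]
- CMH, one stratum: the same with N − 1 in place of N as multiplier
- Yates: d replaced by d − N/2

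A table is rejected if the statistic exceeds 3.841. The true size is the sum of the product-binomial probabilities of all rejected tables, maximised over the common DCR. Enumerating every table gives these maximum sizes in percent:

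| Arms | Pearson | CMH | Fisher | Boschloo |
|---|---|---|---|---|
| 6 v 6 | 6.76 | 3.86 | 0.63 | 3.86 |
| 6 v 7 | 6.67 | 4.05 | 2.25 | 4.05 |
| 6 v 8 | 6.59 | 6.59 | 1.98 | 4.27 |
| 6 v 9 | 4.28 | 4.28 | 3.46 | 4.28 |
| 7 v 7 | 5.74 | 5.74 | 1.29 | 2.37 |
| 7 v 8 | 4.65 | 4.65 | 3.52 | 3.94 |
| 7 v 9 | 8.07 | 4.96 | 2.51 | 4.41 |
| 8 v 8 | 7.68 | 5.34 | 2.13 | 2.79 |
| 8 v 9 | 5.25 | 5.25 | 3.38 | 3.38 |
| 9 v 9 | 5.70 | 3.28 | 2.10 | 3.28 |

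Pearson exceeds 5% in eight of ten pairs, CMH in four (6 v 8, 7 v 7, 8 v 8, 8 v 9), and the exact tests in none. The Yates-corrected chi-square is at most 2.1% in every pair.

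**Step 3: dependence on the true DCR.** At 7 versus 9 the Pearson size is 8.1% at a DCR of 0.5, 7.3% at 0.7, 5.1% at 0.8 and 1.5% at 0.9. Over all ten pairs it is at most 5.3% at 0.8 and 1.9% at 0.9.

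**Step 4: the same data under each test.**

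- 6/6 versus 3/6: d = 18, m = 9, so X² = 12 × 324 / (6 × 6 × 9 × 3) = 4.0. CMH = 4.0 × 11/12 = 3.67. The p-values are Pearson 0.046, CMH 0.056, Boschloo 0.068, Fisher 0.18.
- 6/8 versus 2/8: d = 32, m = 8, so X² = 16 × 1024 / (8 × 8 × 8 × 8) = 4.0. CMH = 4.0 × 15/16 = 3.75. The p-values are Pearson 0.046, CMH 0.053, Boschloo 0.077, Fisher 0.13.

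In nine of ten pairs (all but 6 v 9), some tables are significant by Pearson and not by Boschloo. Fisher's conservatism therefore does not explain the whole gap.

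**The case against.** The strongest case on the other side has four parts.

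First, the 8.1% belongs to one variant of one of the two named tests. CMH, which the protocol names first, has a maximum of 4.96% at that same pair and does not call either example in the working significant. With a Yates correction the inflation disappears. This stands. A reader might infer that 8.1% is the error rate of the planned comparison, or that both tests are anti-conservative throughout. The protocol supports neither, since it fixes neither the test nor the variant. CMH alone still reaches 6.6%, though, and the open choice is itself part of the problem.

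Second, the worst case needs a DCR in the middle of its range. DCR counts stable disease as a success, so a high rate is plausible, although the protocol gives no figure. This also stands and limits the practical size. Equally, a minimum expected count of 5 is a rule of thumb and not a limit of validity: 6 versus 9 breaks it and still keeps the size at 4.3%.

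Third, the variant and a sparse-table fallback are details that an analysis plan often settles. That would answer the point if the protocol were silent, but it names the two tests and no exact one.

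Fourth, the comparison has a larger weakness: the arms are formed by resectability, so even an exact p-value would not compare treatments. That is true. It lowers the stakes without making the reported p-value correct.

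A reader might also take the absence of a named interval method for DCR ("DCR with 95% CI are calculated") as an error, given the exact interval for the DLT rate. It is not one: the method is merely unspecified, and a statistical analysis plan can supply it.

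**Conclusion.** The point holds in limited form. At the planned arm sizes, the tests fixed for the DCR comparison can exceed a 5% error rate: up to 8.1% for uncorrected Pearson and up to 6.6% for unstratified CMH, with the excess mainly at mid-range DCR. They can also give opposite answers on the same table, with no rule for choosing. A corrected chi-square would err the other way.

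These sizes rest on a two-sided 5% level and an unstratified CMH test, neither of which the protocol states. It would be too strong to say that any reported DCR p-value misses its nominal level; that depends on the arm sizes, the variant and the true rate. Severity is low: DCR is secondary in a phase I study of 12-18 patients, and no dose, stopping or other decision uses its p-value.

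**What to change.** If a between-arm DCR comparison is kept, replace the choice of two tests with one exact test named in advance, in section 15.5.3 and the synopsis, and state the significance level and sidedness. Boschloo's unconditional exact test is suitable. The sizes above use the version that doubles the smaller one-sided p-value; ordering tables by the two-sided Fisher p-value raises the maximum to 4.96%, still within 5%, so the version should be named too. Fisher's test is also valid but more conservative (0.6-3.5%).

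The cost is one sentence in two places, with no extra patients or data. The downside is mild conservatism, so a few borderline tables lose significance. A Clopper-Pearson interval for DCR in each arm would be a reasonable optional addition.
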